### Statistical methods

All data will be collected in a dedicated database and analyzed by the ST. We will perform intention to treat (ITT) and per-protocol analysis. We will perform ITT analysis by considering the mother-child pair lost after randomization: (1) all missing values of the primary outcome will set to the worst outcome in both groups (equal-case scenario ITT) and (2) missing values of the primary outcome will set to the worst outcome in the Group 1 and to the best outcome in the Group 2 (worst-case scenario ITT). The worst outcome will be defined as the occurrence of ≥1 atopic condition at 24 months, in the offspring; the best outcome will be its opposite. The secondary outcomes will be evaluated using per-protocol analysis. The Kolmogorov-Smirnov test will be used to determine whether variables are normally distributed. Descriptive statistics will be used to summarize baseline characteristics. The Student *t*-test will be used to compare mean values of continuous variables for approximating a normal distribution. For non-normally distributed variables, the Mann-Whitney *U* test will be used. The χ^2^ test or Fisher exact test will be used, when appropriate. We will use a binomial regression model (BRM) to estimate the incidence of the main outcome, i.e., at least one atopic condition at 24 months, in the offspring. The response variable of the BRM will be the presence of at least one atopic condition at 24 months (0 = no; 1 = yes), and the predictor will be the treatment cohort (0 = Group 1; 1 = Group 2). To evaluate the effect of potential confounders on the main outcome, we will add each of them separately to the aforementioned BRM and we will evaluate the changes in the estimated risk ratios. The evaluated potential confounders will be sex (0 = female; 1 = male), age (months), cesarean delivery (0 = no; 1 = yes), born at term (0 = no; 1 = yes), breastfed for at least 2 months (0 = no; 1 = yes), weaning (months), siblings (number), exposed to passive smoking (0 = no; 1 = yes), mother smoked during pregnancy (0 = no; 1 = yes), and exposed to pets (0 = no; 1 = yes), drug use (0 = no; 1 = yes), antiseptics exposure (0 = no; 1 = yes), lifestyle (0 = rural; 1 = urban), dietary habits (0 = low MD-adherence; 1 = medium MD-adherence; 2 = high MD-adherence) and pollution exposure (0 = no; 1 = yes). BRM is among the most commonly suggested methods to report the results from randomized controlled trials with binary outcomes. Regression modeling allows adding baseline co-variables to increase the precision of the estimate and better control for potential confounders. Comparisons of taxa or gene abundance between groups will be carried out using pairwise Wilcoxon tests. Statistical significance of pangene prevalence will be verified through Fisher’s test with multiple-hypothesis testing corrections *via* the false discovery rate (FDR). Machine learning-based classification analysis will be done using the MetAML package (30) and by considering random forests (RFs) as back-end classifier for all the results. Results will be obtained through a fivefold cross-validation and averaged on 20 independent runs. To evaluate whether the significant associations for the cord blood analysis primarily reflect maternal adherence to MD, additional models adjusted for cord blood DNA methylation of the same CpG site and for miRNAs will be evaluated when examining the association between DNA methylation/miRNAs and childhood allergic sensitization. For DNA methylation, using a reference methylation Quantitative Trait Loci (QTL) library, we will evaluate the genetic control of methylation for the top 30 associated CpG sites identified from the mid-childhood meta-analysis for atopic sensitization, environmental and food allergen sensitization. We leveraged genetic-epigenetic information from the ARIES large-scale genome-mQTL analysis, which included 1,000 mother-child pairs^2^ (31). mQTL comparisons will be focused on the *cis* position (i.e., a genetic variant within ±500 Kb of a methylation locus) measured from cord blood, and with MAF ≥5%. The level of significance for all statistical tests will be two-sided, *p* < 0.05. An integrative approach that combines multi-omics data together with integrated clinical data analysis will be performed. Multivariable linear regression will be used to analyze associations differentially methylated regions in cord blood DNA with clinical measures of offspring. All significance values will be corrected to take into account the effect of multiple comparisons, using the Bonferroni adjustment. All analyses will be performed with Stata 16.1 (Stata Corporation, College Station, TX, USA), SAS^®^ version 9.4 (SAS Institute, Inc., Cary, NC, USA) and R version 3.4.1.

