### Study outcomes

The main study outcome will be the evaluation of the effect of MD during pregnancy on the occurrence of allergic disorders at 24 months of age in the offspring.

Secondary study outcomes will include the evaluation of:

–women MD-adherence score (Med Diet Score);–maternal weight gain and pregnancy complications (including gestational diabetes, arterial hypertension, gestosis, cholestasis, premature rupture of membranes (PROM), placental abruption, post-partum anemia, post-partum hemorrhage);–perinatal complications (including intrauterine growth retardation (IUGR), small-for-gestational-age infant (SGA), large-for-gestational-age infant (LGA), preterm delivery, and fetal malformation) and neonatal birth weight;–body growth indices and occurrence of infectious diseases and chronic non-transmissible conditions (obesity, autoimmune diseases, malignancies, neuropsychiatric disorders) in the first 2 years of age in the offspring;–mother-child pair GM metagenomic and metabolomic features;–exclusive and overall breastfeeding duration and breast milk composition;–epigenetic modulation of genes involved in the regulation of immune system and metabolic pathways in the offspring;–child MD-quality Index score (KIDMED).

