### Interventions

All enrolled women will receive, by the CT gynecologists, recommendations about the importance of an adequate energy intake, optimal weight gain during pregnancy based on pre-pregnancy Body Mass Index (BMI) (17) and hygiene rules for the prevention of major foodborne illnesses during pregnancy according to the guidance provided by the Italian Ministry of Health (18). They were also recommended to walk ≥30 min/day. All enrolled women will be instructed on how to complete the 7-day food diary by the RT dietitians.

Only for women enrolled in the Group #1, a nutritional counseling will be provided by the RT dietitians. The RT dietitians will deliver the nutritional counseling over three face-to-face sessions, which will include a session at enrollment (8–13 GW), and two further sessions after 3 months from enrollment (14–28 GW) and after 6 months from enrollment (29–40 GW). The nutritional counseling will be based on a Mediterranean-style Diet. The key components of this diet will include the use of extra virgin olive oil as main cooking fat (at least four tablespoons/day), high intake of vegetables (two servings/day), fruits (three servings/day) (avoiding juices) and wholegrain cereals (three servings/day), three servings of skimmed dairy products/day, 2–3 servings of legumes/week, three servings of fish/week, three servings of nuts and seeds/week, drink at least two liters of water daily, a low consumption of red meat and processed meat, avoidance of refined grains, processed baked goods, pre-sliced bread, soft drinks and fresh juices, fast foods, and precooked meals.

Furthermore, after delivery, the CT will encourage women of both groups to breastfed wherever possible, to not avoid dietary food allergens during breastfeeding, to avoid the use of regular cow’s milk formula as supplementary feed for breastfed infants in the first week of life, and to introduce complementary feeding from 4 to 6 months of age, according to the European Academy of Allergy and Clinical Immunology guidelines for allergy prevention (19).

The decision to interrupt the study participation may take place at any time even without providing any explanation or justification, it will not entail any penalty, loss of benefits or loss of legal rights for mother-child pair and the mother-child personal data will always remain confidential.

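### Every secondary outcome is assigned to per-protocol analysis only, so those comparisons give up the protection of randomisation; how much bias follows depends on a per-protocol set that the article does not define

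*Protocol article*

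**What the plan says.** The Statistical methods section opens with a general statement, "We will perform intention to treat (ITT) and per-protocol analysis", which ties neither analysis to an outcome. It then gives two intention-to-treat rules, and both concern the primary outcome alone: "all missing values of the primary outcome will set to the worst outcome in both groups (equal-case scenario ITT", and "missing values of the primary outcome will set to the worst outcome in the Group 1 and to the best outcome in the Group 2". The secondary outcomes get one sentence: "The secondary outcomes will be evaluated using per-protocol analysis". No other section gives them an as-randomised analysis.

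The Study outcomes section shows what that sentence covers. The list includes "women MD-adherence score (Med Diet Score"), "maternal weight gain and pregnancy complications (including gestational diabetes, arterial hypertension, gestosis, cholestasis" and others), and perinatal complications including "preterm delivery, and fetal malformation", as well as child growth, breastfeeding, microbiome and epigenetic measures.

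Under Interventions, counselling goes to Group 1 only, in three face-to-face sessions: one at enrolment (8–13 gestational weeks, GW), then "two further sessions after 3 months from enrollment (14–28 GW) and after 6 months from enrollment (29–40 GW"). Under Data and sample collection, follow-up visits in the same two later windows are scheduled for all participants, at 12-week intervals.

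**The concern.** A per-protocol set is formed by conduct or events after randomisation. Once women or children are removed on that basis, the remaining groups are no longer those that randomisation made comparable. A difference between them can then reflect who was removed.

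Two features of this trial make that more than a formality. First, only Group 1 has counselling to comply with, so any criterion based on sessions or on following the diet would act on one arm. Second, some secondary outcomes are bound up with compliance. The Med Diet Score measures adherence to the diet. Preterm delivery can come before the last session and so prevent it from taking place.

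At stake are almost all the maternal, perinatal and child results other than allergy. The introduction offers the trial as randomised evidence in a field of conflicting observational studies. Secondary results from a set selected on behaviour would lose part of that advantage.

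**Working it through.** **The plan's own figure.** The only related number is 138 pairs per group, which this point does not dispute. With 30% versus 15%, two-sided alpha 0.05 and power 0.80, the unpooled formula gives n = (1.960 + 0.842)² × (0.30×0.70 + 0.15×0.85) / 0.15² = 117.7. Dividing by 1 − 0.15 for drop-out gives 138.5, which agrees with 138. The change proposed below leaves it alone.

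The article gives no per-protocol definition, so everything that follows is illustration under stated assumptions. The true group effect is zero throughout.

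**Preterm delivery: does the last session come before the birth?**

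Inputs from the article: enrolment at 8–13 GW; third session six months later, within 29–40 GW; visits every 12 weeks. Assumptions: enrolment uniform over 8–13 GW; gestational age at birth Normal with mean 39.2 and SD 1.8 weeks in both arms; Group 1 women who deliver before session 3 are excluded; nobody is excluded from Group 2.

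- Overall preterm rate: P(birth < 37) = Φ((37 − 39.2)/1.8) = Φ(−1.22) = 11.1%.
- Group 1 per-protocol rate, for session time S: P(S < birth < 37) / P(birth > S), with numerator and denominator each averaged over S.

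| Timing of session 3 | S (GW) | Group 1 | Group 2 | Ratio |
|---|---|---|---|---|
| Six months as 26 weeks | 8+26 to 13+26 = 34–39 | 5.4% | 11.1% | 0.49 |
| Two 12-week intervals | 8+24 to 13+24 = 32–37 | 9.3% | 11.1% | 0.84 |
| Uniform over the stated window | 29–40 | 8.1% | 11.1% | 0.73 |
| Early in the window | 29–34 | 11.1% | 11.1% | 1.00 |

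If both arms must attend the same visit, the same births leave each arm. Both rates are then understated, but no false difference appears.

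A second route avoids the gestational-age model. If a fraction f of Group 1 preterm cases is excluded and none in Group 2, with true rate p in both, the apparent risk ratio is (1 − f)/(1 − pf). At p = 8% this gives 0.77, 0.52 and 0.27 for f = 25%, 50% and 75%. The value of f is unknown.

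**Med Diet Score: if the set is defined by adherence.**

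Assumptions: SD 2 points; the lowest-scoring fraction e of Group 1 is excluded as non-adherent; a random 15% is excluded from Group 2; 138 per arm before exclusions. The mean of Group 1 then rises by SD × φ(z_e)/(1 − e), where z_e is the e-quantile of the standard normal distribution. The false-positive rates come from 4,000 simulated trials.

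| Excluded from Group 1 | False difference (points) | False-positive rate (nominal 5%) |
|---|---|---|
| 5% | 0.22 | 17% |
| 10% | 0.39 | 38% |
| 15% | 0.55 | 63% |

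If the set means completers or attenders instead, the score does not define its own analysis set. Only ordinary selection remains, of unknown size.

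**The case against.** The strongest reply is that the per-protocol set is undefined, and its definition is commonly left to a fuller document. The article describes intention to treat as a way of handling pairs lost after randomisation by imputing their outcomes. Read against that, per-protocol may simply mean pairs not lost, analysed without imputation. On that reading the sentence is close to an observed-case analysis as allocated, and the fault is largely one of labelling. It is also true that nothing makes attendance at three sessions a condition of analysis, that Group 2 has scheduled visits in the same windows, and that the primary outcome has its own intention-to-treat rules.

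Much of this stands, and it limits what can be said about bias. A reader might infer that the Med Diet Score comparison is circular as planned, that the preterm rate in Group 1 would be spuriously halved, or that every secondary result must favour Group 1. The article supports none of these outright. Circularity needs an adherence-based set. The halving needs attendance required in Group 1 alone and a session 26 weeks after enrolment; the 12-weekly schedule gives 9.3% against 11.1%, and a common visit requirement gives no difference. The direction for the other outcomes is not determined.

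The reply does not remove the core point. Choosing per-protocol for the secondary outcomes is a positive statement in the text, not a detail left open. The general sentence naming both analyses does not override the later, specific one.

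**Conclusion.** The point holds in a conditional form. It is certain that the article assigns all secondary outcomes to per-protocol analysis and specifies intention to treat for the primary outcome only. That gives up the protection of randomisation for these comparisons, and one-arm counselling makes asymmetric exclusions possible.

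The size is not established. For preterm delivery it runs from no distortion to roughly a halving, under an assumed gestational-age distribution and depending on the attendance rule and the session timing. For the Med Diet Score it could be a false difference of about 0.2 to 0.5 points, if the set is adherence-based, the SD is 2 and 5–15% of Group 1 is excluded. The primary analysis and the 138 per group are untouched.

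**What to change.** Replace the sentence on secondary outcomes in Statistical methods with:

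> *Secondary outcomes will be analysed as randomised, in all randomised women or their children with the outcome observed; per-protocol results are supportive only.*

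Add that pregnancy and perinatal complications will be reported for every randomised woman with data, whatever her attendance or diet.

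The cost is one sentence, best settled before database lock. No new data are needed, and the sample size does not change. The downside is that estimated effects may be smaller than in a per-protocol analysis.

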### Data and sample collection

At baseline, after the first evaluation by the RT and the collection of written informed consent form, the CT will collect the following variables in a dedicated chart: anamnestic and clinical features, personal and anthropometric data, socio-demographic factors, gestational age, allergies, number of cohabitants, pets, sports activities, use of drugs, smoking exposure, education level, family and living conditions. At enrollment a validated questionnaire on MD-adherence (Med Diet Score) and a 7-day food diary (five weekdays and two weekend days) will be collected. The 7-day food dairy data will be analyzed using specific software (Winfood–Medimatica Srl) by a dietitian. The intake of drugs, dietary supplements, pre-, pro-, and synbiotics will be recorded in the same chart. Then, the RT will schedule for each participant follow-up visits every 12 weeks from the enrollment (8–13 GW), then at 14–28 GW and at 29–40 GW. During these visits the CT will perform a full physical examination, anamnestic and clinical data collection, stool sampling (at least 3 g), 7-day food diary collection, Med Diet Score assessment. Each item assigns a score of 0 or 1, with a total score ranging from 0 to 14. The three categories of adherence to MD are divided in ≤5 (low), 6–9 (medium), ≥10 (high) score. Furthermore, to ensure and encourage the completion of the 7-day food diary, one week before each visit, the RT will remind the women by a phone call to fill in the food diary daily for the following week and to return them at the following visit. At delivery a cord blood sample (at least 10 ml) and a breast milk sample (collected within 24 h after delivery) (3 ml) will be collected. All neonatal clinical features will be evaluated by CT. After delivery, for all babies a follow-up visit will be planned every 3 months for the first 12 months of life and then every 6 months until the age of 2 years. At each visit the following procedures will be adopted by CT: full anamnestic and clinical evaluation, body growth assessment, occurrence of allergic disorders, occurrence of other conditions, 7-day food diary, child Mediterranean Diet Quality Index score (KIDMED) evaluation, stool sampling (at least 3 g). At each visit the persistence of breastfeeding will be also assessed and a breast milk sample will be eventually collected (3 ml). In addition, Skin Prick Testing using main pediatric allergens will be performed at 12 and 24 months. All collected data and documents will always remain confidential.

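### Breastfeeding duration falls under a t-test or Mann-Whitney default that cannot use pairs lost while still breastfeeding; analyse it as time to cessation, and base the milk comparison on the 24-hour sample

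*Protocol article*

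**What the plan says.** Study outcomes lists, among the secondary outcomes, "exclusive and overall breastfeeding duration and breast milk composition".

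Statistical methods gives a general rule for continuous variables and names no particular outcome. The Student t-test "will be used to compare mean values of continuous variables for approximating a normal distribution"; the next sentence begins "For non-normally distributed variables, the Mann-Whitney" and names the U test. The same section states: "The secondary outcomes will be evaluated using per-protocol analysis". Its missing-value rules are confined to the primary outcome, for example "all missing values of the primary outcome will set to the worst outcome in both groups". Taxa and gene abundances are compared by Wilcoxon tests. No time-to-event method or censoring rule appears.

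Data and sample collection plans child visits "every 3 months for the first 12 months of life and then every 6 months until the age of 2 years". At delivery there is "a breast milk sample (collected within 24 h after delivery"; at later visits, "the persistence of breastfeeding will be also assessed and a breast milk sample will be eventually collected".

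**The concern.** Breastfeeding duration is a time to an event. For a pair lost while still breastfeeding, the minimum duration is known and the end is not. A two-sample test on one number per pair offers two ways out: leave the pair out, or record last contact as the day breastfeeding stopped. The first discards observed time. The second enters a false end date and shifts the group difference if loss is unequal. Unequal loss is conceivable here, because only Group 1 receives counselling (Interventions) and participants know their group (Allocation and blinding).

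Milk raises a related question. After the first sample, milk can come only from mothers still breastfeeding, a subset formed after randomisation and defined by another secondary outcome. A later difference in composition could then reflect who continued rather than what was eaten.

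**Working it through.** **Inputs from the article.** 138 pairs per group, drop-out up to 15% (Sample size calculation), 1:1 allocation, follow-up to 24 months. The 138 serves only as the arm size. It is reproduced by 7.849 × (0.21 + 0.1275) / 0.15² = 117.7, and 117.7 / 0.85 = 138.5. The article gives no figure for breastfeeding.

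**Assumptions.** Median durations of 6 and 8.5 months; loss uniform over 0–24 months and unrelated to duration; all loss after delivery.

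**1. How many pairs are affected.** For exponential durations with mean μ = median / ln 2, let M = μ(1 − 0.5^(24/median)), the mean duration truncated at 24 months. The share lost while breastfeeding is 0.15 × M / 24.
- Median 6: μ = 8.656, M = 8.656 × 0.9375 = 8.115; share = 5.1%.
- Median 8.5: μ = 12.263, M = 12.263 × 0.8587 = 10.531; share = 6.6%.

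The average is about 6%. Without loss, 0.5^(24/6) = 6% and 0.5^(24/8.5) = 14% are still breastfed at 24 months.

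**2. Last contact counted as cessation, no true effect.** A lost pair's mean recorded duration is μ(1 − M/24). Median 6: 8.656 × (1 − 8.115/24) = 5.729, which is 8.115 − 5.729 = 2.386 months too short. The false group difference is this shortfall times the difference in loss:
- 10% vs 25%: 0.15 × 2.386 = 0.36 months.
- 5% vs 25%: 0.20 × 2.386 = 0.48 months.

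At a median of 8.5 months the shortfall is 10.531 − 6.882 = 3.649, giving 0.55 and 0.73 months. With equal loss the difference is zero.

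**3. Dropping pairs.** Dropping every lost pair gives no bias under these assumptions; in simulation the Mann-Whitney type I error stayed near 0.05. Dropping only those whose end is unknown removes long durations. With a true median of 7.0 months and 15% drop-out, the median among those kept was 6.65; with 25% vs 5% drop-out, type I error was 0.076, against 0.048 for log-rank.

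**4. Power.** Simulated, 138 per arm, medians 8.5 vs 6 months. The ranges cover repeated runs of 1,500 to 3,000 trials.

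| Durations | Loss | Mann-Whitney, completers | Log-rank |
|---|---|---|---|
| Exponential | 15% | 62–63% | 76–79% |
| Exponential | none | 68–69% | 77–80% |
| Log-normal (log SD 1) | 15% | 72–75% | 72–76% |
| Log-normal (log SD 1) | none | 80% | 75% |

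A second exponential setting (median 7, hazard ratio 0.7, 15% loss) gave 65% vs 76%. Most of the exponential gap remains with no loss, so it comes from proportional hazards rather than censoring.

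**5. Later milk.** Suppose the diet has no effect on composition and composition has correlation ρ with a latent tendency to continue. With proportion p continuing, the mean among continuers is ρ·φ(Φ⁻¹(p))/p in SD units.
- 40% vs 40%: bias 0.
- 40% vs 50%, ρ = 0.2: about 0.03 SD.
- 30% vs 50%, ρ = 0.4: 0.4636 − 0.3192 = 0.14 SD.

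From 138 × 0.85 ≈ 117 retained per arm, 20–50% continuing leaves about 23–58. Power for a 0.5 SD difference falls from 0.97 to between 0.47 (20% vs 30% continuing) and 0.72 (40% vs 50%).

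**The case against.** The strongest reply is that no sentence assigns the t-test or Mann-Whitney to these outcomes. The article is condensed, and an analysis plan that is not shown may give breastfeeding duration its own method. It is true that the link is inferred. Even so, the default is stated for continuous variables without exception, secondary outcomes are put in a per-protocol set, and duration falls under both as written. A stated default that fits an outcome badly is more than a detail left out.

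Three stronger readings are tempting, and the documents do not support them.
- A reader might infer that the tests need a complete value from every child. They do not: follow-up ends at a common 24 months, so Mann-Whitney can rank children still breastfed then as ties at the top. Exclusive duration is hardly touched by that cut-off, since complementary feeding is advised from 4 to 6 months (Interventions); loss is its main source of censoring.
- A reader might infer that the default costs power. The log-normal rows show no gain from log-rank.
- A reader might infer that later milk comparisons are biased. The article does not expressly specify one, and bias needs continuation both to differ by arm and to relate to composition. Nothing in the article shows that the diet lengthens breastfeeding.

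The bias in duration is also modest: 0.36 months is about 0.05 of an SD of some 6.8 months, and the article anticipates no difference in loss between arms. Finally, pairs lost before delivery contribute no breastfeeding time under any method.

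**Conclusion.** The point holds in limited form. Read as written, the default cannot use pairs lost while still breastfeeding except by dropping them or giving them a false end date. About 6% of pairs are affected under the assumed medians and 15% loss. The shift in means is about 0.4 to 0.5 months at a 6-month median, larger at longer medians, and arises only if loss differs by arm and last contact is taken as cessation. The case for time-to-event analysis rests on using every pair's observed time without that false date, not on a promised gain in power. For milk after the first sample, the difficulty is what is being compared (composition among continuers), and no choice of test removes it. All breastfeeding rates and arm-specific losses here are assumptions. Only secondary outcomes are concerned, so the priority is low to moderate.

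**What to change.** State in Statistical methods, or in the analysis plan, that exclusive and overall breastfeeding duration are analysed as time to cessation: Kaplan-Meier curves with a log-rank test or Cox model, censored at last contact or 24 months. Use an interval-censored version if only breastfeeding status at visits is known, since visits are 3 or 6 months apart. The set should be all randomised pairs with a live birth followed after delivery, as an explicit exception to the per-protocol rule.

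For milk composition, name the sample taken within 24 hours of delivery as the between-group comparison. Report later samples descriptively among mothers still breastfeeding, with the number per arm at each visit.

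The cost is a change of wording. Breastfeeding status and milk are already collected, and the listed software (Stata, SAS, R) can do the analysis. The downside is that results are given as a median duration or hazard ratio instead of a mean difference.

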## Methods and analysis

### Study settings

The study will involve four tertiary gynecology and neonatology centers located in the Campania region in Italy. The annual number of births at each center is >1,500.

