### Allocation and blinding

The randomization and sequence allocation will be performed according to a computer-generated randomization list by building a stratified randomization with permutated block-randomization, stratified by maternal body mass index (BMI) (<25, 25–29.9, and ≥30 kg/m^2^), and parity (1 or >1), in an allocation ratio of 1:1 in blocks of 4–6. The Group #1 will receive standard obstetrical and gynecological follow-up and nutritional counseling to promote MD provided by certified dietitians, and the Group #2: will receive standard obstetrical and gynecological follow-up alone. Due to the nature of the RCT design, participants and RT will be aware of the group assignment. Whereas the allocation to Group #1 or Group #2 will remain unknown to the CT and ST.

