### Sample size calculation

Based on the results of the EUROPREVALL cohort (29), reporting a cumulative incidence for allergic diseases of 30%, and on the results of a previous pilot study performed at our center (unpublished data) showing a drop-out rate to this kind of intervention up to 15%, we estimated that 138 mother-child pair per group will be needed to detect a reduction in cumulative incidence of at least one allergic disease at 24 months from 30 to 15%, with a power of 0.80 at an alpha level of 0.05 (Pearson’s Chi-square, two-tailed test).

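### Randomisation is stratified by BMI and parity but the primary model contains treatment alone, and the baseline Med Diet Score goes unused behind a normality pre-test: a small, conservative loss of precision that wording can repair

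*Protocol article*

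**What the plan says.** Under Allocation and blinding, the protocol article specifies permuted blocks of 4 to 6 at a 1:1 ratio, "stratified by maternal body mass index (BMI") in three classes and by parity in two, which gives six strata. Centre is not named as a stratification factor, although Study settings states: "The study will involve four tertiary gynecology and neonatology centers".

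Under Statistical methods, the response in the primary model is the presence of at least one atopic condition at 24 months, "and the predictor will be the treatment cohort (0 = Group 1; 1 = Group 2"). Fifteen potential confounders are then added one at a time to see how the risk ratio moves. BMI, parity and centre are not among them; the nearest item is number of siblings. The same section remarks that baseline covariates in a regression improve precision.

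For continuous variables: "The Kolmogorov-Smirnov test will be used to determine whether variables are normally distributed". A t-test follows if normality is accepted and a Mann-Whitney test if not. No baseline or stratum term is mentioned. Under Data and sample collection, however: "At enrollment a validated questionnaire on MD-adherence (Med Diet Score") is collected, and the same 0 to 14 score is reassessed at the two later pregnancy visits.

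**The concern.** Stratified blocks make the two arms more alike on BMI and parity than simple randomisation would. An analysis that ignores the strata computes its standard error as if that balance had not been imposed. If the strata predict the outcome, the standard error is too large, the confidence interval too wide and the test conservative. The trial pays for stratification and does not collect the benefit.

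The continuous outcomes raise a second, separate issue. A normality pre-test lets the observed data decide whether means or ranks are compared, so the quantity being estimated is not fixed in advance. For the Med Diet Score, the first secondary outcome listed and the direct evidence that counselling changed diet, the comparison also leaves out an enrolment value that is probably its best predictor.

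The article states the response, the predictor, the coding, the covariates and the test-selection rule outright. These are stated choices, not details left to an unseen analysis plan.

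**Working it through.** **1. The plan's own sample size.** Inputs from Sample size calculation: a control risk of 30%, an intervention risk of 15%, drop-out up to 15%, and a test specified "with a power of 0.80 at an alpha level of 0.05 (Pearson’s Chi-square, two-tailed test"). With unpooled variance, n = (1.960 + 0.842)² × (0.30×0.70 + 0.15×0.85) / 0.15² = 7.85 × 0.3375 / 0.0225 ≈ 118 per group. Dividing by 0.85 gives 139, against the stated 138, so the figure reproduces. After 15% loss, 138 × 0.85 ≈ 117 per group remain. The unadjusted test then has power of about 0.788, so there is no slack.

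**2. Primary outcome: cost of ignoring the strata.** The documents give no prognostic strength for BMI or parity, so everything here rests on assumptions: BMI classes 60/27/13%, parity 50/50, four equal centres with modest differences, overall risk 30%. The share of outcome variance explained by the strata is R² = Σ wₖ(pₖ − 0.30)² / (0.30×0.70). The unadjusted standard error is too wide by the factor 1/√(1 − R²), and the true two-sided alpha is about 2[1 − Φ(1.96/√(1 − R²))].

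Strong scenario, stratum weights 0.30, 0.30, 0.135, 0.135, 0.065, 0.065 and risks 0.303, 0.152, 0.458, 0.260, 0.620, 0.405: the sum is 0.0175, R² = 0.0175/0.21 = 0.0835, and the factor is 1/√0.9165 = 1.045.

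| Assumed odds ratios (per BMI class; parity) | Stratum risks | R² | SE excess, complete cases | Approx. true alpha | SE excess, imputed ITT | Power, unadjusted vs stratified |
|---|---|---|---|---|---|---|
| 1.3; 0.7 | 24–43% | 1.41% | 0.7% | 0.048 | 0.4% | 0.780 vs 0.782 |
| 1.5; 0.6 | 21–49% | 3.04% | 1.6% | 0.047 | 1.0% | 0.795 vs 0.799 |
| 2.0; 0.4 | 15–62% | 8.35% | 4.5% | 0.041 | 2.7% | 0.788 vs 0.816 |

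Power comes from 4,000 simulated trials per scenario: 276 randomised, blocks of 4 or 6 within six strata, 15% random loss, unadjusted chi-square against stratified Mantel-Haenszel. The Monte Carlo standard error is about 0.0065. With strata that predict nothing, power was 0.790 unadjusted and 0.783 stratified, which is no real difference.

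The simulated null rejection rates were 0.050, 0.039 and 0.049 unadjusted and 0.054, 0.043 and 0.059 stratified. Their Monte Carlo standard error is √(0.05×0.95/4000) ≈ 0.0034, so the levels are noisy. The unadjusted rate is the lower one in every scenario, as theory predicts.

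**3. Effect of the imputed intention-to-treat analysis.** In the equal-case scenario all missing outcomes become events. With 15% loss unrelated to stratum, the null risk is 0.85×0.30 + 0.15 = 0.405, with variance 0.405×0.595 = 0.241. Between-stratum variance shrinks by 0.85². R² is therefore multiplied by 0.7225 × 0.210/0.241 = 0.63, giving 0.89%, 1.92% and 5.26%. The resulting SE excesses are in the sixth column.

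**4. Med Diet Score.** Let r be the correlation between the enrolment and follow-up scores (not given; 0.5 to 0.7 assumed). Relative variances are 1 for follow-up only, 2(1 − r) for change and 1 − r² for ANCOVA.
- Against follow-up only: 1 − r² = 0.75 at r = 0.5 and 0.51 at r = 0.7, so 25% and 49% less variance.
- Against change: (1 − r²)/[2(1 − r)] = (1 + r)/2 = 0.75 and 0.85, so 25% and 15% less variance.

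**The case against.** The strongest reply is that the effect on the primary outcome is close to nil and errs on the safe side. That stands. The upper end of the range needs stratum risks from about 15% to 62%, a spread nothing in the documents supports, and the complete-case figures shrink further once missing outcomes are imputed as planned. A reader might infer that the primary analysis is invalid or that the false-positive rate is inflated. The documents support neither: an unadjusted test after stratified blocks is conservative.

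A reader might also infer that leaving out centre makes the standard error wrong. It does not, because centre is not a stated stratification factor; omitting it forgoes possible precision only. Follow-up visits take place on site, which makes centre a reasonable covariate, but the article does not say where counselling is delivered.

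Nor can the ANCOVA gain be extended to the secondary outcomes in general. Maternal weight gain is already a change from a starting value, and offspring growth has no value at randomisation. Even for the Med Diet Score, the article does not say whether the follow-up value or the change is compared. The saving against follow-up only, equivalent to 33% to 96% more participants (1/0.75 and 1/0.51), is therefore an upper range for one outcome at an assumed correlation.

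It can also be said that the plan already has adjusted models, with siblings standing in for parity. This helps little. Covariates enter singly, BMI never enters, and several listed variables arise after randomisation (caesarean delivery, term birth, breastfeeding, weaning).

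**Conclusion.** The point holds as a modest, no-cost improvement. The primary model does not reflect the stratified design. Under assumed stratum effects its standard error is about 0.7% to 4.5% too wide in complete cases and about 0.4% to 2.7% in the equal-case intention-to-treat analysis, with a complete-case power loss of about 0 to 3 points. The loss is zero if BMI and parity do not predict allergy. The direction is conservative, so no positive finding is put in doubt.

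The normality pre-test and the missing baseline term are a separate weakness. For the Med Diet Score the avoidable variance is 25% to 49% if follow-up values are compared and 25% to 15% if changes are compared, at correlations of 0.5 to 0.7. Both sets of figures rest on assumptions, because the documents give neither the prognostic strength of the strata nor the correlation.

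**What to change.** Define the primary model as treatment + BMI stratum + parity stratum. Report an adjusted risk ratio and risk difference, using standardisation or Poisson regression with robust errors if the log-binomial model does not converge. Keep the treatment-only model as a sensitivity analysis. Centre may be added as an optional precision covariate.

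Drop the Kolmogorov-Smirnov step. Analyse the Med Diet Score, and any other continuous outcome with a baseline value, by ANCOVA or a mixed model with the baseline value and the strata. For continuous outcomes without a baseline value, adjust for the strata only.

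The cost is wording in the analysis plan. BMI class and parity are known at randomisation and the enrolment score is already collected, so no new data are needed.
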